### Secondary outcomes

Secondary behavioural outcomes will be analysed as a binary (*yes/no*) response to behavioural questions that have been adapted from existing questions used to evaluate other NSW Health programs [37]. These include:

*Type of toothpaste used*. This secondary behavioural outcome considers whether a parent is using fluoride toothpaste according to current guidelines [9]. This will be calculated based on the response to the question: “What type of toothpaste do you put on our child’s toothbrush?” [37]. A *yes* response will be considered for “Children’s fluoride toothpaste”, “Standard fluoride toothpaste” or, “Prescribed toothpaste” and a *no* response to those answering, “Non-fluoride toothpaste” and “Don’t know/unsure.”*Frequency of sugared beverage consumption for the child*. This secondary behavioural outcome considers the number of sweet beverages a child has per week based on cut-offs determined by current Australian guidelines [38]. This will be calculated based on the response to the question “How often does your child drink sugar-sweetened drinks (such as soft drinks, cordials, sports drinks, flavoured milk, fruit juices, energy drinks or iced teas?)” A *yes* response will be considered for “Rarely” or “Never” and a *no* response for those answering, “Every day” “A few times a week” and “Don’t know/unsure.”*Frequency of sweet food consumption for the child*. This secondary behavioural outcome considers the dietary behaviours of the child related to the frequency of sweet foods per week based on recommendations from the WHO guidelines for the consumption of sugar [39]. This will be calculated based on the response to the question “How often does your child eat sweet foods like chocolates, sweetened cereal, ice cream, flavoured milk or yoghurt, biscuits, cakes, pastries, or snack/muesli bars?” A *yes* response will be considered for “Rarely” or “Never” and a *no* response for those answering, “Every day” “A few times a week” and “Don’t know/unsure.”*Bedtime routines related to the frequency and timing of milk consumption at night*. This secondary behavioural outcome measure considers the specific risk behaviour of consuming milk before or during sleeping hours as outlined in the WHO’s ECC report [9]. This will be calculated based on the response to the question “How often does your child go to bed with milk in a sippy cup or bottle?” A *yes* response will be considered for “Rarely” or “Never” and a *no* response for those answering, “Every day” “A few times a week” and “Don’t know/unsure.”*Frequency of water consumption*. This secondary behavioural outcome measures the positive behaviour of frequently consuming water. This will be calculated based on the response to the question “How often does your child drink water?” A *yes* response will be considered for “Every day” and a *no* response for those answering, “A few times a week” “Don’t know/unsure” “Rarely” or “Never.”*Oral Health self-efficacy*. To provide some information on the construct of oral health self-efficacy, we will collect a standardised set of six questions on each of the three target behaviours (oral hygiene, diet and bedtime routines) that were adapted from previously published literature [40]. The six questions consider capability (physical capability and psychological i.e. knowledge capability), opportunity (physical opportunity, social opportunity), and motivation (reflective motivation, and automatic motivation) [40,41]. These questions draw upon the COM-B framework which itself draws upon the Health Beliefs Model (HBM) and the Theory of Planned Behaviour (TPB) [42,43]. The total oral health self-efficacy measure for each target behaviour (oral hygiene, diet and bedtime routines) will be analysed by a composite measure out of 60. Secondary analysis for each question includes a binary measure which will be dichotomously categorised where a score of 8 or more on a 10-point Likert scale is considered a *yes* and a score below 8 is considered *no*.

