
### Statistical analysis

Our statistical analysis will follow an intention-to-treat principle. A full pre-specified statistical analysis plan will be developed and finalised before study completion, data lock and analysis. Normally distributed continuous variables will be expressed as means with standard deviations. Non-normally distributed variables will be expressed as medians and interquartile ranges. Binary variables will be presented as proportions with their 95% confidence intervals (CI). The proportion of parents who meet the primary outcome of toothbrushing twice a day with toothpaste at baseline and 3 months will be presented descriptively by treatment groups. An odds ratio of brushing their child’s teeth twice a day with toothpaste at 3 months comparing treatment vs. control (reference group) will be estimated with a 95% CI using a logistic regression model adjusting for whether parents are toothbrushing twice a day with toothpaste at baseline and stratification variables. All dichotomous secondary outcomes will be analysed using the same logistic regression model and continuous secondary outcomes will be analysed using linear regression. A statistical significance level of 0.05 will be used. Interaction between treatment and pre-specified covariates will be conducted to explore the heterogeneity of our results. Sub-group analyses will be conducted for treatment modality (DGA vs. non-DGA), and site (tertiary vs. non-tertiary). No multiplicity adjustments will be performed for secondary outcomes as they are exploratory by nature. We will not be conducting further interim analyses with stopping guidelines. All analysis will be undertaken using R.

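### The only item-level self-efficacy analysis stated cuts each of 18 ten-point items at 8 or more, giving no reason and losing information; the composites and the primary outcome are unaffected

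*Protocol article*

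**What the plan says.** Under Secondary outcomes, the self-efficacy entry of the protocol article describes a "standardised set of six questions on each of the three target behaviours", namely oral hygiene, diet and bedtime routines. The six questions cover capability, opportunity and motivation, two each. The total for each behaviour "will be analysed by a composite measure out of 60".

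The next sentence goes down to the single question: "Secondary analysis for each question includes a binary measure", which is "dichotomously categorised where a score of 8 or more on a 10-point Likert scale is considered a" yes, with any lower score a no. No reason for 8 is given.

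The Statistical analysis section then supplies the models: "All dichotomous secondary outcomes will be analysed using the same logistic regression model and continuous secondary outcomes will be analysed using linear regression". It adds that "A statistical significance level of 0.05 will be used", and on multiplicity: "No multiplicity adjustments will be performed for secondary outcomes as they are exploratory by nature".

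**The concern.** A ten-point answer is collected from each parent at baseline and at three months, and the stated item-level analysis keeps only which side of 8 it falls on. A parent who moves from 2 to 7 counts as unchanged; one who moves from 7 to 8 counts as a success. The logistic model described for the primary outcome adjusts for baseline yes/no status. If the same model is carried over to the items, the baseline score is cut as well, a further loss that is not quantified below.

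At stake is the component detail. Each composite adds capability, opportunity and motivation within a behaviour, so it cannot show which of them moved. The item analysis is the only randomised comparison in the article that could. As stated, it is imprecise, depends on one unexplained threshold, and could yield 18 p-values among which a chance result is not unlikely.

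**Working it through.** **Inputs from the article.** Six questions for each of three behaviours; ten-point items cut at 8; significance level 0.05; 53% against 78% on the primary outcome; 80% power; 25% drop-out; 1:1 allocation. The article gives no item distribution, so p, the share of parents scoring 8 or more, is an assumption and is varied.

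**1. The plan's own sample size.** With a two-sided 0.05 level and pooled variance (mean proportion 0.655), the number per arm is

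[1.960 × √(2 × 0.655 × 0.345) + 0.842 × √(0.53 × 0.47 + 0.78 × 0.22)]² / 0.25² = 55.6, so 56 per arm and 112 in total.

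112 / 0.75 = 149.3, or 150 with equal arms. The stated 150 is reproduced, and 56 completers per arm is used below.

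**2. Item count.** 6 × 3 = 18. Each composite has a maximum of 6 × 10 = 60, which agrees with the article. A move from 2 to 7 on one item adds 5 points to the composite and a move from 7 to 8 adds 1, so the composites keep what the item cut discards.

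**3. Information kept by the cut.** For a normal score, the efficiency of a yes/no cut relative to comparing means is φ(z_p)² / [p(1 − p)].

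| Share at 8 or more | Kept | Lost | 112 parents count as |
|---|---|---|---|
| 50% | 0.637 | 36% | 71 |
| 30% or 70% | 0.576 | 42% | 64 |
| 80% | 0.490 | 51% | 55 |
| 90% | 0.342 | 66% | 38 |
| 95% | 0.224 | 78% | 25 |

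The formula is symmetric, so 10% gives the same loss as 90%.

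**4. Sensitivity to normality.** With a latent normal score rounded to 1–10 and piled up at the ends (latent mean 6 to 10, SD 1.5 to 2.5), efficiency runs from 0.696 down to 0.316, a loss of about 30% to 68%.

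**5. The same loss as power.** With 56 per arm, the standardised difference detectable with 80% power on the uncut score is (1.960 + 0.842) × √(2/56) = 0.53. Shifting the intervention arm by that amount on the normal scale and then cutting gives:

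| Control share at 8 or more | Intervention share | Power after the cut |
|---|---|---|
| 50% | 70.2% | 59% |
| 70% | 85.4% | 50% |
| 80% | 91.5% | 41% |
| 90% | 96.5% | 28% |

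**6. Eighteen tests at 0.05 with no true effect on any item.** Expected false positives: 18 × 0.05 = 0.9, whatever the correlation. Chance of at least one if independent: 1 − 0.95¹⁸ = 60%. In a simulation with equally correlated test statistics it is 51%, 40% and 28% at correlations of 0.3, 0.5 and 0.7.

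**The case against.** The strongest reply is that the main self-efficacy analysis is not cut at all. A reader might infer from the rule of 8 that the self-efficacy outcome itself is dichotomised. The article does not support that: the three composites come first, and continuous secondary outcomes go to linear regression. This stands, and it confines the point to the item level.

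A reader might also infer that 18 unadjusted tests threaten the trial's error rate. They do not. Secondary outcomes are openly declared exploratory and unadjusted, and no confirmatory claim rests on them. The fix would still leave 18 unadjusted intervals; it changes how they are read, not how many there are.

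The testing itself is partly inference. The article also says that binary variables will be shown as proportions with confidence intervals, and self-efficacy is a single line in Table 2. The logistic route is the literal reading of the Statistical analysis section, but nowhere is it said that each item will be labelled significant or not. Likewise, the word used for the item analysis is inclusive, so item scores may also be reported; the article states no such analysis.

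Two further readings go too far. The cut cannot be called arbitrary, because the source of the items and the full questionnaire are not at hand; what can be said is that the article gives no reason. Nor can the scale-up decision be said to depend on the items: Study aim and Process evaluation assign that question to fidelity, reach, and interviews and focus groups.

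What survives is that a stated method discards collected information, and a declaration of exploratory status explains the lack of adjustment but does not justify the cut.

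**Conclusion.** The point holds as a low-priority improvement to the exploratory item-level results. The loss of about 36% to 66% assumes roughly normal scores with 10% to 90% of parents at 8 or more. It would be nearer 30% for some discrete distributions, and 78% if scores were normal and 95% of parents reached 8. None of these figures comes from the article. The 60% chance of at least one false positive requires independent tests. Six questions about one behaviour are unlikely to be independent, so about 28% to 60% is the fair range, and then only if each item is in fact tested.

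**What to change.** In the self-efficacy entry under Secondary outcomes, and in the analysis plan the article promises before data lock, replace the item-level rule as follows:

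- Analyse each of the 18 items on its 1–10 score with the linear regression already planned for continuous secondary outcomes, with arm, the item's own baseline score and the stratification variables as covariates.
- Report the 18 mean differences with 95% confidence intervals, marked exploratory and without significance labels.
- Keep the share scoring 8 or more as a descriptive percentage by arm, with the reason for 8 if there is one.

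The composites stay as they are. The cost is a change of wording: the data are already collected, and the sample size and primary analysis do not move. The downside is that a mean difference is slightly less intuitive than a percentage, which the descriptive share covers.

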
### Statistical analysis

Our statistical analysis will follow an intention-to-treat principle. A full pre-specified statistical analysis plan will be developed and finalised before study completion, data lock and analysis. Normally distributed continuous variables will be expressed as means with standard deviations. Non-normally distributed variables will be expressed as medians and interquartile ranges. Binary variables will be presented as proportions with their 95% confidence intervals (CI). The proportion of parents who meet the primary outcome of toothbrushing twice a day with toothpaste at baseline and 3 months will be presented descriptively by treatment groups. An odds ratio of brushing their child’s teeth twice a day with toothpaste at 3 months comparing treatment vs. control (reference group) will be estimated with a 95% CI using a logistic regression model adjusting for whether parents are toothbrushing twice a day with toothpaste at baseline and stratification variables. All dichotomous secondary outcomes will be analysed using the same logistic regression model and continuous secondary outcomes will be analysed using linear regression. A statistical significance level of 0.05 will be used. Interaction between treatment and pre-specified covariates will be conducted to explore the heterogeneity of our results. Sub-group analyses will be conducted for treatment modality (DGA vs. non-DGA), and site (tertiary vs. non-tertiary). No multiplicity adjustments will be performed for secondary outcomes as they are exploratory by nature. We will not be conducting further interim analyses with stopping guidelines. All analysis will be undertaken using R.

### Data management plan

All data will be collected at baseline and at a 12-week follow-up (Fig 1). An enrolment log will be maintained by a delegated member of the research team with the express permission of the coordinating principal investigator (CPI). This log will be stored on LHD servers. Access to the LHD server is restricted by password, those with access must also be employees/contingency workers of that LHD. Only the CPI and delegated researchers will have access to the complete and final data set from all sites, and only available on REDCap.

Baseline data will include demographic information, baseline oral health behaviour, and self-efficacy delivered through the REDCap platform [44]. The REDCap system is an online secure capture data collection and management tool for research use. Our study will use REDCap to collect baseline and post-intervention data. REDCap has been provided by the Office for Health and Medical Research for the use of researchers in NSW Public Health LHDs, networks, and pillars. REDCap is hosted in the eHealth AWS cloud, maintained by eHealth, and supported by the Office for Health and Medical Research. It is secured, and backed up daily, where privacy and confidentiality considerations of participants are protected.

Whilst most questionnaires and PICF forms are provided electronically, there may be a small number of participants requesting hard copies. Once the hard copies are obtained, study staff at each site will log in to the REDCap database with their unique username and password to enter data. Staff will only have access to data collected at their specific site. Only coded data will be analysed. Only the chief investigator and principal investigator will have access to all study data. Hard copies of consent forms and questionnaires will be stored in lockable filing cabinets in a restricted access room, only accessible by project staff, and restricted by swipe access provided by the sites.

All data for this study will be collected from the individuals themselves. No additional data will be gathered from medical/ health records. Following the NHMRC guidelines on the management of data and information in research, paper and electronic study information, including the consent forms and questionnaires, will be securely stored until 5 years after the completion of the study. Electronic data will be permanently deleted from servers and hard copy documentation shredded and disposed of in secure confidential bins provided by hospital sites. The destruction of the data will follow processes following the University of Sydney Research Data Management processes in alignment with the NHMRC guidelines.

For the process evaluation, where Zoom or online telephone links are sent, meetings will be password protected. Further confirmation of the receipt of the PICF will be provided on the recordings. All data from the recordings will be stored on a secure encrypted server of the University of Sydney’s Research Data Store and deleted from any device. Any quantitative metrics to assess fidelity will be analysed by R [45] or SPSS v22. All qualitative data will be analysed using NVivo version 12.0 [46] coded data will be analysed in themes qualitative methodologies, following a framework analysis approach [47].

### Safety considerations

Whilst it is unlikely that there will be adverse effects from the text message intervention, our protocol ensures participants’ safety by providing a relevant contact person including a senior clinician-researcher at each of the sites and a contact person at the patient experience units to address complaints related to the study. Parent participants can opt out of the program at any time. Parents can do this by texting back “STOP”. Once they do this the participants will no longer receive messages from the text messaging platform. However, to withdraw from the study they will need to contact the principal investigator at their site to complete the withdrawal form.

The TextCare™ platform will be centrally monitored by a clinician-researcher. This centrally monitored system enables adherence to the intervention’s pre-set delivery algorithm and data collection sequence set out in this protocol. If any participant requires clinical assistance for their child’s oral health during the study period, they will be provided contact details to their nearest NSW public dental clinic. Additionally, if the patient’s condition worsens from an acute dental abscess leading to a facial swelling, they will be provided the contact details for their nearest paediatric emergency service. After the patient contacts the public dental service, an appointment will be provided according to the current eligibility policies in place within NSW public dental services [27]. The details of a senior clinician researcher for the specific sites will also be provided on the PICF. A log of the participants who have stopped the intervention, withdrawn, or responded to messages seeking clinical care will be managed by the delegated clinician researcher using data from the REDCap and TextCare™ platforms.

### Process evaluation

A mixed methods process evaluation of the *SmilesUp* text messaging intervention will be conducted to determine the fidelity, reach, barriers, and enablers to scale the program. Quantitative analysis of fidelity will be measured by exposure (number of text messages delivered and received) and engagement (participant responsiveness to the text messages) [48]. Reach will be measured by the diversity of the participants, and locations using the baseline demographic variables of the study.

To complement the quantitative data; qualitative data collection and analysis will also be conducted to determine the barriers, enablers, and opportunities to scale future text message programs. A convenience and purposive sample reflective of the ethnic and cultural diversity of parents that participated in the program. Framework analysis will be used to analyse qualitative data collected through focus groups and semi-structured interviews [32]. Using the snowballing recruitment technique, we will recruit until the saturation of themes is obtained and anticipate this to be around 20 participants. Similarly, to understand the health system barriers, enablers, and opportunities to scale the program, health professionals (clinician/ academic/ public health professional) will also be invited to attend separate focus groups or semi-structured interviews either conducted in person or via telephone or video call. The focus groups and semi-structured interviews will be conducted by a trained researcher. Those attending in person will be reimbursed for their travel and parking expenses.

### Ethical considerations

Ethics approval has been obtained from the Western Sydney Local Health District Human Research Ethics Committee 2022/ETH01920. The study is currently recruiting with data collection completion anticipated for September 2024. Any amendments to the study will be made in consultation with all principal and site investigators and the Western Sydney Local Health District Human Research Ethics Committee who provided the original approval. This includes changes to eligibility criteria, and analyses, or the addition of sites. Our original protocol version titled *SMILESup_protocol_V2_181122* which included the intervention development as a separate phase [31] was approved by the ethics committee on the 1^st^ of December 2022. Our current protocol version titled *SMILESup_protocol_V5_260923*, focused on the addition of two new study sites and was approved by the ethics committee on the 10^th^ of October 2023. This trial has also been prospectively registered with the Australia and New Zealand Clinical Trials Registry. The ANZCTR is an online register of clinical trials taking place in Australia and New Zealand. It is one of the first three trial registries to be recognised by the World Health Organization International Clinical Trials Registry Platform (WHO ICTRP) as a Primary Registry. Our registration number for the study is ACTRN12623000325606.

## Discussion

The widespread use of mobile phones presents an opportunity for dental researchers, health system managers, policymakers, and health professionals to consider mHealth programs that directly support parents in managing modifiable behavioural risk factors related to ECC [14]. Current preventive disease management approaches for ECC focus on behavioural-focused interventions in clinical settings like Motivational Interviewing (MI) which has shown mixed results and is resource intensive [49]. These MI methods also rely on additional face-to-face interactions, which may not be feasible for time-constrained parents seeking convenient, home-based, nudge-type interventions to establish oral health habits [24].

To address this gap, the *SmilesUp* mobile health intervention has been co-designed to engage parents in managing ECC risk in a semi-personalised way that integrates with their daily lives. This single-blinded RCT protocol outlines the rigorous methods used to test the effectiveness of the intervention with a diverse range of parents in NSW. If successful *SmilesUp* offers an innovative, and cost-effective program to support behaviour alongside the family’s journey of receiving clinical care. By choosing to utilise low-cost and simple text messages, our mode of delivery seeks to minimise the digital health literacy divide [50]. Our mHealth program is not prohibitive to parents who cannot afford to download apps that use a lot of data. It is also not reliant on poor internet connectivity which may affect parents in rural and regional areas. Therefore, text messages were chosen as a modality that we could use to provide the *SmilesUp* text messages equitably and at scale.

We anticipate that the program will improve oral health behaviours positively and increase the parent’s oral health self-efficacy in the medium-short term. Through a comprehensive process evaluation reaching a broad range of families accessing public dental care including DGA across metro, rural and regional local health districts, it also seeks to understand the implementation process by understanding what works, for whom and in which context.

Future research designs that are interoperable with electronic oral health record systems will enable the measurement of longer-term ECC oral health clinical outcomes from these programs, including decayed missing and filled teeth (dmft/DMFT) and dental general anaesthetic service utilisation patterns for the families who have received the text message program. Equally this program may be integrated with other successful digital public health programs for parents related to lifestyle habits for childhood development [51,52] Finally, our outlined methods in this protocol paper and learnings from our process evaluation could inform similar development, adaption and translation of mHealth programs for patients of different cultural backgrounds, ages with other oral or general health conditions.

